# 7.2 METHODS OF ANALYSIS

Serum vitamin D measurement will be undertaken by Liquid chromatography–mass spectrometry (Glasgow RI Biochemistry). Bowel tissue (rectal biopsy) measurement of vitamin D will be undertaken using a novel assay system reported in the literature (Immunodiagnostic Systems, Scottsdale, AZ, USA).

Genotyping will be undertaken to identify risk alleles using Illumina OmniExpress Exome GWAS arrays which provides comprehensive cost-efficient genotyping of loci of interest and pre and post active treatment gene expression assessed using Illumina HT-12 array and validated using qRT-PCR. Statistical comparison of pre- and post-treatment gene expression will be undertaken using the Mann-Whitney U test.

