| DESIGN | Through NHS clinical services in colorectal surgery and oncology, patients will be identified and recruited from surgical wards or surgical/oncology out-patient clinics. A sample of participants with and without a new or previous diagnosis of colorectal cancer will be included for comparison.  Participation will consist of two events in the majority of participants. Firstly a in the surgical ward or clinic lasting no longer than 20 minutes in which the research will be discussed and informed consent gained. A blood sample will be taken prior to the conclusion of recruitment and a rectal biopsy taken using a rigid sigmoidoscopy which may or may not be required as part of their routine clinical assessment. Participants will be asked to take pharmaceutical grade vitamin D tablets for 3 months. After 12 weeks of vitamin D supplementation, a final blood sample and rectal biopsy will be taken.  **If patients would like to contribute but cannot or would prefer not to take vitamin D, or cannot return for future sampling, a single sampling will be offered. This participant would undergo blood sampling and rectal biopsy as above. After this no further events would occur.** |
| AIM | To identify the underlying mechanism by which Vitamin D reduces colorectal cancer risk. |
| OBJECTIVES | To demonstrate the effects of vitamin D supplementation on serum vitamin D levels.  To demonstrate dynamic changes in gene expression in response to vitamin D.  To demonstrate the mechanism underlying the gene-environment interaction of vitamin D, susceptibility genetic variants (risk genes) and colorectal cancer. |
| OUTCOME  MEASURES | *Primary outcome:* Change in expression of genes in bowel tissue in response to vitamin D  *Secondary outcomes:*  Change in expression of genes in bowel tissue in response to vitamin D dependent on participant genotype  Change in serum vitamin D level in response to vitamin D supplementation.  Change in tissue vitamin D level in response to vitamin D supplementation. |
| ELIGIBILITY | Aged 16 years or over.  Resident of the UK. |

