# 3. STUDY DESIGN

# 3.1 STUDY OUTCOME MEASURES

PRIMARY OUTCOME – the change in expression of genes relevant to colorectal cancer risk in response to vitamin D supplementation.

SECONDARY OUTCOMES - the genotypic associations with changes in gene expression in response to vitamin D supplementation, the change in serum and tissue vitamin D level after vitamin D supplementation.

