# 5.6 LABORATORY SAMPLES

A blood sample will be taken into 2 lithium heparin tubes and 2 EDTA tubes by venepuncture (~30mls). The rectal biopsy will be taken into RNA preservative. If patients are required to undergo further endoscopy for clinical reasons, we will request a study biopsy to be taken during this. All samples will be anonymised through use of an identifying number and will be processed by the Wellcome Trust Clinical Research Facility (WTCRF), Western General Hospital, Edinburgh. The research team will make arrangements for the safe transport of samples to the WTCRF through the use of a pre-paid sealed transport system. Following 12 weeks of Vitamin D supplementation repeat blood (~30mls) and rectal biopsies will be taken.

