# 7. STATISTICAL ANALYSIS

# 7.1 SAMPLE SIZE

Due to the novel nature of this study and methodology, a convention power calculation was not possible. Using genes which have been shown to be of particular interest to the relationship between vitamin D and bowel cancer, our department has calculated the mean expression of these genes to be ~7.5 units on gene expression (HT-12 microarray) analysis. An analysis of 10 genes would require a significance level adjusted for the effect of multiple testing (hence p<0.005) and with a conventional power level set at 80%. The maximum standard deviation on expression data was 0.42. Assuming 1 standard deviation (i.e. more than twice the observed between subject variation the number of subjects required to detect a change of 4 units (approximately 1.5 fold) would be n=8 and 8 units (approximately 2 fold) would be n=5. Assuming 2 standard deviations (i.e. more than four times the observed between subject variation, the number of subjects required to detect a change of 4 units (approximately 1.5 fold) would be n=57 and 8 units (approximately 2 fold) would be n=18.

*In vitro* pilot work to date has demonstrated a 5-7 fold increase in the expression of one gene of particular interest in response to vitamin D treatment which supports the above calculations.

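### The primary before/after comparison of gene expression names an independent-samples test (Mann-Whitney U) for repeat biopsies from the same people; it ignores the pairing, is conservative, and loses power that grows with the within-person correlation

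*Protocol*

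**What the plan says.** The primary outcome (Protocol 3.1) is "the change in expression of genes relevant to colorectal cancer risk in response to vitamin D supplementation". It is measured on repeat samples from the same people. The Study Summary, under Design, describes a biopsy at recruitment and then: "After 12 weeks of vitamin D supplementation, a final blood sample and rectal biopsy will be taken". Section 5.6 says the same: "Following 12 weeks of Vitamin D supplementation repeat blood (~30mls) and rectal biopsies will be taken".

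Section 7.2 gives the analysis: "Statistical comparison of pre- and post-treatment gene expression will be undertaken using the Mann-Whitney U test". This is the only statistical test that the protocol names, and no section names a paired one.

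Section 7.1 sets the threshold: "An analysis of 10 genes would require a significance level adjusted for the effect of multiple testing (hence p<0.005"), "with a conventional power level set at 80" per cent. It gives sample sizes of 8 and 5 (changes of 4 and 8 units, SD 1) and 57 and 18 (the same changes, SD 2). It names no test for these numbers. The only observed SD is between subjects: "The maximum standard deviation on expression data was 0.42". Neither the SD of the within-person change nor the correlation between a person's two biopsies is given.

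**The concern.** The Mann-Whitney test treats the pre and post values as coming from different people. Stable differences between people, which cancel in a within-person difference, stay in its error term. Its reference distribution is also too wide when the pairs are positively correlated, so the real type I error falls below the nominal 0.005 and true changes are harder to detect.

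This affects the primary outcome of a small study with a strict per-gene threshold. A change that a paired analysis would detect could be reported as no change. Because the protocol fixes the test, an analysis plan faithful to it would inherit the problem.

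**Working it through.** **Inputs.** Per-gene alpha 0.005 = 0.05/10 (7.1; sidedness not stated, two-sided assumed). Power 80% (7.1). Sample sizes 8, 5, 57 and 18 (7.1). The within-person correlation ρ is not in the protocol, so it is varied as an assumption. Data are taken as normal, with equal SD σ before and after.

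**Step 1: the plan's own sample sizes.** A two-sided t-test at 0.005 and 80% power (noncentral t) gives:

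| 7.1 scenario | Stated n | Paired t, literal effect (change/SD) | Two-sample t per group, literal effect | Standardised effect near the stated n | Paired t at that effect | Two-sample t per group at that effect |
|---|---|---|---|---|---|---|
| 4 units, SD 1 | 8 | 5 | 4 | 2 | 8 | 9 |
| 8 units, SD 1 | 5 | 4 | 3 | 4 | 5 | 4 |
| 4 units, SD 2 | 57 | 8 | 9 | 0.5 | 58 | 109 |
| 8 units, SD 2 | 18 | 5 | 4 | 1 | 18 | 29 |

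The stated numbers do not follow from the literal inputs. They are close to a paired t-test at standardised effects 2, 4, 0.5 and 1 (at effect 0.5, n=57 gives 79.8% power). That suggests sizing for a paired design, but the protocol does not say so.

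**Step 2: why ignoring the pairing is conservative.** The variance of the within-person difference is 2σ²(1−ρ). An independent-samples comparison works as if it were 2σ², so the ratio of actual to assumed variance is 1−ρ. The two-sided critical value at 0.005 is 2.807, so the actual error is roughly P(|Z| > 2.807/√(1−ρ)):

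- ρ=0.3: 2.807/0.837 = 3.36, error about 0.0008.
- ρ=0.5: 2.807/0.707 = 3.97, error about 0.0001.

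Simulation of the Mann-Whitney test agrees: about 0.0005-0.001 at ρ=0.3 and about 0.0001 at ρ=0.5.

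**Step 3: power, with the change fixed in SDs of the within-person difference.** Simulated at two-sided 0.005:

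| ρ | n=18, 1 SD: Mann-Whitney | n=18, 1 SD: paired t | n=57, 0.5 SD: Mann-Whitney | n=57, 0.5 SD: paired t |
|---|---|---|---|---|
| 0 | 84-86% | 82-83% | about 80% | 79-81% |
| 0.3 | about 65% | 82-83% | about 60% | 79-81% |
| 0.5 | about 42% | 82-83% | about 35% | 79-81% |
| 0.7 | about 14% | 82-83% | about 9% | 79-81% |

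**Step 4: the same question with the change fixed at 1 between-subject SD.** The standardised paired effect is then 1/√(2(1−ρ)). A paired t-test needs 31, 23, 18 and 12 participants at ρ = 0, 0.3, 0.5 and 0.7. An unpaired t-test needs 29 per occasion at every ρ.

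**Step 5: literal 7.1 effects.** At n=8 (4 units, SD 1), n=57 (4 units, SD 2) and n=18 (8 units, SD 2), Mann-Whitney and paired t both have power of about 100% at ρ = 0, 0.5 and 0.8. At n=5 (8 units, SD 1), paired t has about 100% and Mann-Whitney has none, because its smallest two-sided p is 2/C(10,5) = 2/252 = 0.0079.

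**Step 6: the floor of the obvious substitute.** The smallest two-sided p of the Wilcoxon signed-rank test is 2/2ⁿ: 0.0625 at n=5, 0.0078 at n=8 and 0.0039 at n=9. It needs at least 9 pairs to reach p<0.005.

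**The case against.** The strongest reply is that the size of the loss is not known. It depends on ρ, which the protocol does not give; at ρ=0 nothing is lost, and at the literal 7.1 effects nothing is lost for n=8, 18 or 57. The steep fall in Step 3 also depends on scaling. Holding the change at 1 SD of the difference makes the raw change shrink as ρ rises. With the change held at 1 between-subject SD and n=18, Mann-Whitney power stays at about 43-45% for ρ from 0 to 0.7, while paired t rises from about 46% to 97%. The cost is then power forgone rather than a collapse. Finally, the error is conservative under positive correlation, so it does not create false positives. All of this stands, and it limits what can be said about size. It does not make the test suitable for paired data.

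Three stronger readings are tempting and not supported:

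- A reader might infer that most of the power is lost. About half or more is lost only from ρ of roughly 0.5 upwards, and only for effects of the size in Step 3.
- A reader might infer that 7.1 proves the study was sized for a paired t-test. The section names no test, says a conventional calculation was not possible, and matches only after the stated effects are replaced by other standardised ones.
- A reader might infer that single-sample participants will enter the pre-treatment group. Section 7.2 refers to expression before and after active treatment, and section 2 gives single samples a separate correlation objective. Nothing says that the two are pooled.

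**Conclusion.** The point holds and should be corrected before analysis. Section 7.2 names an independent-samples test for a primary outcome measured twice on the same people. That mismatch follows from the text alone and needs no assumption.

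The consequence is conditional. For positive ρ the test is conservative and loses power, increasingly so as ρ rises. With n=18 and a change of 1 SD of the within-person difference, the loss against paired t is nil at ρ=0, about 17 to 18 percentage points at 0.3, about 40 at 0.5 and nearly 70 at 0.7. These figures rest on an assumed ρ, normal data and two-sided testing. At the literal 7.1 effects the loss is negligible except at n=5, where significance at 0.005 is unattainable. That the 7.1 numbers do not follow from their stated inputs is a separate matter.

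**What to change.** In section 7.2, replace the Mann-Whitney test with a paired analysis of each participant's change on the log2 expression scale: a paired t-test, or a moderated paired linear model with participant as block. Apply it to intervention participants who have both pre- and post-treatment samples.

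State how the 18-week schedule (section 5.11, Figure 2) is handled. It takes two pre-treatment biopsies, six weeks apart, so a simple post-minus-pre difference is not defined there. One option is to keep both in the model with participant as block.

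Use the Wilcoxon signed-rank test only as a sensitivity analysis, and note that it cannot reach two-sided p<0.005 with fewer than 9 pairs, so it could not work at the n=5 or n=8 in section 7.1.

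The cost is a few sentences in 7.2. No new data, visits or samples are needed.

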# 8. ADVERSE EVENTS

The Investigator is responsible for the detection and documentation of events meeting the criteria and definitions detailed below.

Full details of contraindications and side effects that have been reported following administration of Vitamin D can be found in the relevant Summary of Product Characteristics (SmPC).

Participants will be instructed to contact their Investigator at any time after consenting to join the trial if any symptoms develop. All adverse events (AE) that occur after joining the trial must be reported in detail in the Case Report Form (CRF) or AE form. In the case of an AE, the Investigator should initiate the appropriate treatment according to their medical judgment. Participants with AEs present at the last visit must be followed up until resolution of the event.

# 8.1 DEFINITIONS

An **adverse event** (AE) is any untoward medical occurrence in a study participant which does not necessarily have a causal relationship with the study intervention.

An **adverse reaction** (AR) is any untoward and unintended response to the study intervention.

A **serious adverse event** (SAE), **serious adverse reaction** (SAR). Any AE or AR that at any dose:

- results in death of the study participant;
- is life threatening*;
- requires in-patient hospitalisation^ or prolongation of existing hospitalisation;
- results in persistent or significant disability or incapacity;
- consists of a congenital anomaly or birth defect;
- results in any other significant medical event not meeting the criteria above.

*Life-threatening in the definition of an SAE or SAR refers to an event where the participant was at risk of death at the time of the event. It does not refer to an event which hypothetically might have caused death if it were more severe.

^Any hospitalisation that was planned prior to randomisation or clearly relating to a pre-existing condition will not meet SAE criteria. Any hospitalisation that is planned post randomisation will meet the SAE criteria.

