# 4.2 EXCLUSION CRITERIA

The inability to provide informed consent.

Under the age of 16 years.

A non-UK resident.

Patients who may be at increased risk from rigid sigmoidoscopy:

- Individuals who are taking anti-coagulation medication.
- Individuals with platelet disease or other bleeding issues.
- Individuals with a history of a significant rectal bleed.
- Suspected or known bowel perforation
- Anal stenosis
- Acute peritonitis
- Colonic necrosis
- Toxic megacolon
- Acute severe diverticulitis
- Diverticular abscess
- Recent colonic surgery
- Anal fissure
- Severe coagulopathy
- Anticoagulant therapy
- Severe thrombocytopenia
- Severe neutropenia

**Patients who may be at increased risk from Vitamin D supplementation would not be included in the intervention arm but could still be included in the single sample arm:**

- Kidney disease
- High levels of calcium in the blood
- Atherosclerosis
- Sarcoidosis
- Histoplasmosis
- Over-active parathyroid gland (hyperparathyroidism)
- Lymphoma
- Currently taking thiazide diuretics, digoxin or other cardiac glycosides
  - Known allergy to nuts ( as peanut oil contained within vitamin D preparations)
  - Female subjects of child bearing age who are not taking effective contraception during the period of the trial

Patients in whom vitamin D levels may be unpredictable

- Individuals already established on supplementary Vitamin D.
- Individuals recently returned to the UK from an overseas holiday.
- Individuals who have recently lived abroad.
- Patients on anti-epileptic medication

Presence of any of the above exclusion criteria will be elicited from relevant patient records including clinical case notes and recent laboratory tests.

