# 8.2 IDENTIFYING AEs AND SAEs

All AEs and SAEs will be recorded from the time a participant signs the consent form to take part in the study untilthe end of the study.

Participants will be asked about the occurrence of AEs/SAEs at every visit during the study. Open-ended and non-leading verbal questioning of the participant will be used to enquire about AE/SAE occurrence. Participants will also be asked if they have been admitted to hospital, had any accidents, used any new medicines or changed concomitant medication regimens.

AEs and SAEs may also be identified via information from support departments e.g. laboratories*.*

Events clearly related to a known underlying medical condition, in particular colorectal cancer, will not be recorded, including but not limited to admissions for planned or emergency surgery, admissions with bowel obstruction or admissions with rectal bleeding.

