### Assessment of Causality

The Investigator will make an assessment of whether the AE/SAE is likely to be related to the study intervention according to the definitions below.

- Unrelated: where an event is not considered to be related to the study intervention.
- Possibly Related: The nature of the event, the underlying medical condition, concomitant medication or temporal relationship make it possible that the AE has a causal relationship to the study intervention. The assessment of causality will be made against the reference safety information found in the Summary of Product Characteristics [last updated 29th June 2013].

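### Sections 8.1 and 8.2 take events in pre-existing conditions out of SAE status by hospitalisation, and out of the safety record, without asking whether the condition worsened or the study contributed

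*Protocol*

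**What the plan says.** The protocol treats an event as serious if, among other criteria, it "requires in-patient hospitalisation^ or prolongation of existing hospitalisation" (8.1). The caret leads to a footnote, under which an admission already planned before randomisation, or one "clearly relating to a pre-existing condition will not meet SAE criteria". The footnote then adds: "Any hospitalisation that is planned post randomisation will meet the SAE criteria". The remaining criteria carry no such mark. They include death, threat to life, disability and an open-ended last item, "results in any other significant medical event not meeting the criteria above".

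Section 8.2 first says that all AEs and SAEs are recorded from the signing of consent until the study ends. It closes with an exception: "Events clearly related to a known underlying medical condition, in particular colorectal cancer, will not be recorded". Its examples, given as non-exhaustive, are admissions for surgery (elective or emergency), bowel obstruction and rectal bleeding. A separate sentence before 8.3 says that an observation is recorded when its status as an AE is in doubt.

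Three other places bear on this. The opening of section 8 requires every AE after joining to be reported in detail. Section 8.1 defines an AE as an untoward occurrence that need not be caused by the intervention. Section 6.1 names perforation, haemorrhage and pelvic sepsis as the major risks of rigid sigmoidoscopy with biopsy, and calls their incidence negligible.

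**The concern.** That an admission relates to an old condition does not rule out that the study made the condition worse. The 8.1 footnote uses the first fact to settle SAE status by hospitalisation and never asks about the second. Section 8.2 uses it to settle whether anything is written down at all.

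The later safety steps depend on that record. The report to the sponsor's office within 24 hours is triggered by an SAE. The ethics committee report needs an SAE that is possibly related and unexpected. The annual safety report lists SARs. An event that is neither serious by definition nor recorded reaches none of them.

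The study samples people with a new or previous diagnosis of colorectal cancer and takes rectal biopsies from them, so events of the kind 8.2 leaves out are foreseeable. A serious aggravation during supplementation, or a bleed after the study biopsy that is put down to known disease, could pass without anyone having documented a view on cause.

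**Working it through.** No arithmetic applies. The check is to follow typical events through the protocol's own steps.

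**Inputs.** The AE duty (opening of section 8), the AE and SAE definitions with the footnote (8.1), the recording rule (8.2), the assessments of seriousness and causality and the upgrade power (8.4), and the reporting rules (both sections numbered 8.5).

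| Event after consent | AE by 8.1? | SAE by hospitalisation? | Recorded under 8.2? | Reaches 8.4 and 8.5? |
|---|---|---|---|---|
| Emergency admission because a known condition has worsened on vitamin D | Yes | No, by the footnote's first sentence | No, if clearly related to the condition | No record to assess or report |
| Admission for rectal bleeding after the study biopsy, attributed to known colorectal cancer | Yes | No, same sentence | No, rectal bleeding is a named example | No record to assess or report |
| Admission newly planned after entry for a known condition | Yes, if the event is untoward | First sentence: no. Second sentence: yes | No, planned surgery is a named example | Undetermined |
| As the first row, but life-threatening | Yes | Serious anyway, under an unmarked criterion | No, 8.2 makes no exception for seriousness | Serious by 8.1, unrecorded by 8.2 |

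**Row 1.** The section 8 duty and the exception in 8.2 cannot both be followed. Seriousness in 8.4 is judged by reference back to 8.1, so the footnote governs whatever the investigator thinks about cause. The protocol sets no explicit order of steps, but no causality judgement can be documented for an event that is not recorded.

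**Row 2.** Section 6.1 recognises haemorrhage as a risk of the study procedure, while 8.2 names rectal-bleeding admissions among the events to leave out. In addition, 8.4 judges relatedness to the study intervention against the product information for the supplement, so the biopsy is not clearly covered even when an event is recorded.

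**Row 3.** The footnote's two sentences give opposite answers. Both date from randomisation, and the protocol describes none, so the cut-off is undefined. Section 8.2 dates recording from consent.

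**Row 4.** The unmarked criteria keep the event serious on paper, but 8.2 still tells the investigator not to record it.

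**The case against.** The strongest defence is that this is a deliberate and ordinary choice. In a colorectal population, surgery, obstruction and bleeding are expected, and reporting each within 24 hours would produce forms of little value. The word clearly leaves room for judgement: an admission thought to be due to vitamin D might not be seen as clearly due to the old illness. Screening narrows the exposed group, since "Patients who may be at increased risk from Vitamin D supplementation would not be included in the intervention arm", and 4.2 also excludes people with a history of significant rectal bleeding or on anticoagulants. The Chief Investigator may upgrade an AE to an SAE or SAR.

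Most of this is fair, and it limits the point. It does not remove it. A wish to avoid expedited reports supports relief from the 24-hour report, not a ban on recording. The upgrade power acts on an AE that somebody has recorded. The rule for doubtful cases concerns whether something is an AE, not a plain worsening of a known condition.

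Two stronger readings may tempt a reader and should not be adopted.

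- One might infer that 8.4 contradicts 8.1 and 8.2, because it says "The nature of the event, the underlying medical condition, concomitant medication or temporal relationship make it possible that the AE has a causal relationship". That text lists the underlying condition as one factor in judging cause. It does not make an event reportable.
- One might picture kidney disease or high calcium missed at screening and then aggravated. The non-recording rule in 8.2 covers only a known condition, so while the condition remains unknown that rule does not apply.

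**Conclusion.** The point holds as a faulty stated rule. The 8.1 footnote removes SAE status by hospitalisation, and 8.2 removes recording, with no test of worsening and none of causality. This conflicts with the duty to report all AEs and with a definition of an AE that is neutral as to cause.

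A reader might go further and infer that such an admission can never be an SAE or SAR. The text does not support that: the footnote marks only the hospitalisation criterion, its second sentence makes admissions planned after entry serious, and a recorded AE can be upgraded. The accurate statement is that these events can largely escape recording, causality assessment and reporting.

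Nor can a size be given. The protocol states no rate of serious events and no share arising in pre-existing conditions, so any figure for the under-count would rest on invented shares. The conclusion assumes only that investigators follow 8.1 and 8.2 as written. It concerns safety capture and leaves the gene-expression outcome untouched.

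**What to change.** - **8.1, footnote.** Limit the exemption to admissions planned before consent, or elective admissions for a pre-existing condition that has not worsened since consent. Replace randomisation with consent as the cut-off. Rewrite the second sentence so that the two no longer give opposite answers for an admission planned after entry.
- **8.2, last paragraph.** Record events in a known condition that worsens after consent, flag them as disease-related, and assess causality both to the supplement and to the study procedures. Bring the paragraph into line with the opening of section 8.
- **8.5, reporting of SAEs.** State that only disease-related events judged unrelated to the supplement and the study procedures are exempt from the 24-hour report.

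The cost is short edits in three sections, a flag on the AE and SAE forms, and some extra disease-related forms. The exemption in 8.5 keeps most of the expedited-reporting burden away.
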